### Calculation of the sample size

The estimation of the sample size and statistical power for the trial were determined based on the main variable, pain measured through the VAS. Based on a previous study [26] and estimating that patients in the intervention group would have a difference of 15 mm or more in the VAS compared to the control group, differences of at least 5% can be detected with a statistical power of 90% and a significance level alpha α of 0.05. This will require a sample of 24 patients per group, which will result in a total of 72 participants. Therefore, a maximum monitoring loss of 20% will be allowed. To carry out this sample calculation, the G*Power v. 3.1 Software was used.

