The main aim is to study the short- and long-term effects of a PNE tool as a supplement to a multimodal rehabilitation (MR) program in BC patients with persistent pain upon finishing adjuvant treatment to determine its impact on pain, physical function and quality of life. Our hypothesis is that a PNE tool as a supplement to a MR program based on exercise and manual therapy techniques, will be more effective in improving persistent pain in cancer patients than an MR program combined with TBI. This will be compared to a control group.

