## Discussion

The current trial will determine if the application of combined PNE with an MR program presents higher efficacy in reducing pain than the application of this MR program without PNE. Previous studies have demonstrated that the combination of PNE with other therapies such as exercise or dry needling, obtains better results in kinesiophobia and pain than the sum of its parts in chronic neck pain [65, 66]. These findings in PNE are consistent with the results obtained in chronic low back pain and other chronic musculoskeletal pain conditions, in conjunction with usual physiotherapy interventions and exercise, respectively [67, 68]. However, despite these benefits, to our knowledge no intervention has tested the effects of a PNE app within a physical therapy program in a breast cancer population suffering from pain and dysfunction. Furthermore, earlier evidence shows that more research is needed to observe the effects of pain management and healthy lifestyle interventions in cancer survivors [69].

Different studies have shown the efficacy of MR programs (exercise, kinesitherapy and/or manual therapy) in health issues related to pain and dysfunction associated with medical treatment of BC [70–72] or colon cancer [73]. We therefore consider it possible that similar results could be achieved with MR programs in patients who had breast cancer and present with persistent pain. A recent study has piloted the effectiveness of a PNE session in cancer survivors, and they present preliminary but promising results [19]. It seems necessary to design and implement appropriate treatment programs for this specific population. Currently, the cancer population still faces difficulties in receiving optimal treatment programs for their illness or survivorship heaviness and support to maintain a healthy lifestyle [69].

Although participants can also have different levels of PA outside the program. It will be registered with the IPAQ-SF questionnaire and considered for analyses. Even though low adherence levels might be expected from the exercise program, supervision by the physical therapist and social interaction between participants will reinforce adherence and physical function. This could open up the possibility to participants to share their pain coping strategies and all achievements made. In addition, despite there will be participants who will not know how to use the app, they will be taught how to properly use it to benefit the most from PNE.

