The proposed study may help BC patients with persistent pain improve their pain experience, quality of life and provide for more adaptive pain-coping strategies. This protocol could propose an action guide to implement different integral approaches for the treatment of sequelae. If the group that includes PNE sessions proves to be more effective in reducing pain and improving physical function and quality of life than the groups without PNE, this treatment option could be offered to this patient profile and it could be easily implemented in the healthcare systems due to its low costs. Our results will be disseminated through social media, professional conferences and international refereed journals.

We expect moderate effectiveness on pain, physical function and quality of life due to the multimodal approach and the fact that we give the PNE contents 6 months after having undergone surgery and/or have finished adjuvant treatment (radiotherapy and/or chemotherapy). Providing PNE in the early postoperative stage [21], could be a barrier in the process of reconceptualizing pain as having psychological distress and poor cognitive functions (attention and memory) are common in that period [74–76].

Results from the PaiNEd trial will be disseminated in peer-reviewed journals, national and international conferences focused on pain, oncology and rehabilitation. Furthermore, findings will also be available through social media of the research team. Finally, participants and other interested cancer patients will know the final results of the study.

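### The 90% power is derived for intervention versus leaflet-only control and is not shown to apply to the trial's own question, PNE+MR versus TBI+MR

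*Protocol article*

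**What the plan says.** Calculation of the sample size (Methods) bases the trial on the VAS, "estimating that patients in the intervention group would have a difference of 15 mm or more in the VAS compared to the control group". It states that "differences of at least 5% can be detected with a statistical power of 90% and a significance level alpha α of 0.05" and concludes: "This will require a sample of 24 patients per group, which will result in a total of 72 participants". A loss of up to 20% is allowed. The SD is left to a cited earlier study and not given.

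The Intervention section defines three arms: PNE plus MR, traditional biomedical information (TBI) plus MR, and a control group that receives only the TBI leaflet. The Abstract, Intervention and Data analysis sections all use control for that third arm. The TBI+MR arm is described as an intervention group that attends the same MR programme as the first arm.

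The hypothesis at the end of the Introduction is that the PNE tool added to MR "will be more effective in improving persistent pain in cancer patients than an MR program combined with TBI"; a comparison with the control group is then added. The Discussion says the trial will determine whether PNE with MR "presents higher efficacy in reducing pain than the application of this MR program without PNE".

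Data analysis specifies a 3x3 repeated-measures ANOVA with Bonferroni post hoc tests and a significance level of 0.05.

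**The concern.** The contrast used for sizing and the contrast named in the hypothesis are different. The first compares an intervention containing exercise and manual therapy with a leaflet. The second asks what an education app adds when both arms receive the same exercise and manual therapy. A planning difference for the first does not carry over to the second without an argument, and none is offered.

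The Bonferroni post hoc step adds to this. If all three pairs of arms are tested, the hypothesis contrast is judged at 0.0167, whereas the power claim is made at 0.05.

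What is at stake is how the main result will be read. A non-significant PNE+MR versus TBI+MR comparison, in a trial described as having 90% power, could be taken as evidence that PNE adds nothing, when the power of that comparison was never established.

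**Working it through.** **Inputs from the article.** Difference 15 mm on a 100 mm VAS; power 90%; alpha 0.05; 24 per group; allowed loss 20%, so 24 × 0.8 = 19.2, about 19 per group; three arms, equal allocation; Bonferroni post hoc, so 0.05/3 = 0.0167 if all three pairs are tested.

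**Not in the article, therefore assumed.** Two-sided testing; the SD, back-solved below; the increment of PNE+MR over TBI+MR, for which 10 and 7.5 mm are illustrative values.

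**Formula.** For a two-sample t-test with n per group, power = 1 − F(t_crit; df = 2n − 2, λ). F is the noncentral t distribution function, λ = (Δ/SD) × √(n/2), and t_crit is the 1 − α/2 quantile of the central t.

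**Reproducing the plan's figure.** Without an SD, 24 per group cannot be derived forwards. Solving for the SD that gives 90% at 15 mm:

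- If 24 is the evaluable number: df = 46, t_crit = 2.013, λ = 3.31, d = 0.956, SD = 15/0.956 = 15.7 mm.
- If 24 already includes the 20% loss, so that 19 are evaluable: df = 36, t_crit = 2.028, λ = 3.33, d = 1.081, SD = 15/1.081 = 13.9 mm.

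So 24 per group is attainable with an SD of about 14 to 16 mm. The 90% at 15 mm is the starting point of this calculation and confirms nothing by itself.

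**Hypothesis contrast, n = 24.** Here √(24/2) = 3.464. With SD 15.7 mm, 10 mm gives λ = 0.637 × 3.464 = 2.21, and 7.5 mm gives λ = 0.478 × 3.464 = 1.66. With SD 13.9 mm, λ is 0.720 × 3.464 = 2.50 and 0.540 × 3.464 = 1.87. At α = 0.0167, t_crit rises to 2.485.

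| PNE increment (assumed) | α = 0.05, SD 15.7 | α = 0.05, SD 13.9 | α = 0.0167, SD 15.7 | α = 0.0167, SD 13.9 |
|---|---|---|---|---|
| 15 mm | 90% | 96% | 79% | 89% |
| 10 mm | 58% | 69% | 40% | 51% |
| 7.5 mm | 37% | 45% | 22% | 28% |

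**After the allowed loss, n = 19, α = 0.05.** With SD 15.7 mm, power is 82%, 48% and 30% at 15, 10 and 7.5 mm. With SD 13.9 mm it is 90%, 58% and 37%.

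**Size needed for 90% power at α = 0.05.** With SD 15.7 mm, 53 evaluable patients per group at 10 mm and 93 at 7.5 mm. With SD 13.9 mm, 42 and 73.

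**The case against.** The strongest reply is that the 90% could still hold. If PNE on top of MR also yields 15 mm, and the contrast is tested at 0.05 with 24 evaluable per group, the stated power is correct for the hypothesis too. That stands as a possibility. The article does not make the claim, however, and its Introduction describes earlier PNE results as conflicting, including a trial that found no better pain intensity than biomedical education.

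The sizing text speaks of one intervention group although two arms are active, so the first half of the sizing contrast is ambiguous. That also stands. The comparator is not ambiguous: nowhere is the TBI+MR arm called the control group. The comparison with control is itself part of the stated aim, so sizing on it is not irrelevant to the trial.

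The size of any shortfall cannot be fixed from the article. The SD is back-solved, sidedness is unstated (a one-sided test at 0.05 would need d = 0.86 instead of 0.96), and the 10 and 7.5 mm increments are illustrative.

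Three stronger readings are tempting and should be resisted:

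- The Discussion says "We expect moderate effectiveness on pain, physical function and quality of life due to the multimodal approach", and Data analysis labels d of 0.50 to 0.79 as moderate. A reader might join the two and conclude that the authors themselves expect an effect too small for this design. The sentence covers three outcome domains, gives no d, and credits the multimodal approach, which both active arms receive, together with the timing of PNE. It is not a planning effect for PNE+MR versus TBI+MR.
- A reader might predict a significant result against the leaflet and an uninformative PNE result. Without an SD or a difference for the PNE contrast, that cannot be derived.
- A reader might infer that all pairwise contrasts are given equal standing. The article says only that post hoc tests use Bonferroni; a ranking may be in an analysis plan that is not shown.

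**Conclusion.** The mismatch holds on the article's own wording: the sizing contrast is intervention versus leaflet-only control, and the hypothesis contrast is PNE+MR versus TBI+MR. The accurate statement is that the 90% is not shown to apply to the hypothesis, which is weaker than saying that it cannot apply.

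The numerical consequence is conditional. Under two-sided testing with 24 evaluable per group and an SD of 13.9 to 15.7 mm, an increment of 10 mm would be detected with 58% to 69% power at 0.05, and one of 7.5 mm with 37% to 45%. If Bonferroni over three pairs applies, the ranges are 40% to 51% and 22% to 28%. The mismatch itself depends on none of these assumptions.

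**What to change.** - Name PNE+MR versus TBI+MR on VAS, at one prespecified time point, as the primary contrast. Test it at two-sided 0.05 outside the Bonferroni set, with the comparisons against control as secondary. Which time point to use is the sponsor's choice, since the aim covers short- and long-term effects.
- In Calculation of the sample size, say that the 90% refers to intervention versus leaflet-only control, and say which active arm is meant.
- In the same section, give the difference, SD, alpha, loss allowance and resulting power for PNE+MR versus TBI+MR, using the SD from the sponsor's own source study. The back-solved values above should not be written into the protocol.
- Report that contrast's confidence interval as the main result.

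The cost is wording in the protocol and analysis plan. The stated power becomes less favourable and the control comparisons become secondary. The rewording needs no extra patients, but it adds no power either: if the sponsor wants 90% for an increment below 15 mm, the sample size has to be reconsidered.

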### Data analysis

To analyze the results, the statistical program IBM SPSS 26 (IBM Corp., Armonk, NY, USA.) will be used. The descriptive statistics for this study (95% confidence intervals) will use mean and standard deviation (continuous data) or frequencies and percentages (categorical data). The Kolmogorov-Smirnov test will be applied to verify the normal distribution of the variables (p> 0.05). Receiver operating characteristic (ROC) curves will be included to determine the accuracy of the tests. A t test will be used to analyze parametric variables, and a Mann–Whitney U test will be used for nonparametric variables. From the point of view of inferential statistics and to respond to the main objective of this study, an intention-to-treat analysis will be carried out. A 3x3 repeated-measures ANOVA model will be performed using time (baseline, postintervention, follow-up) as a within-subject factor and intervention (first arm, second arm, control) as a between-subjects factor. The Bonferroni test will be used for post hoc analysis. For the study on subgroups with possible differential results, cancer location, type of treatment, elevated tumor stages, age, sex will be used as possible confounding variables in a subsequent multiple regression analysis. A significance level of p value less than 0.05 (P < .05) will be considered. The intergroup effect sizes will be calculated to provide magnitude changes; the effect size will be estimated using Cohen’s d (0–0.19, negligible; 0.20–0.49, small; 0.50–0.79, moderate; ≥0.8, large).

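### The sample-size paragraph claims 90% power for a 5% difference while assuming 15 mm (15% of the VAS), and sets the 90% at an alpha and contrast that are not those of the planned pairwise tests

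*Protocol article*

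**What the plan says.** Calculation of the sample size, in the protocol article, bases the size on VAS pain. It supposes that "patients in the intervention group would have a difference of 15 mm or more in the VAS compared to the control group", and concludes that "differences of at least 5% can be detected with a statistical power of 90% and a significance level alpha" of 0.05. It continues: "This will require a sample of 24 patients per group, which will result in a total of 72 participants". The next sentence reads "Therefore, a maximum monitoring loss of 20% will be allowed". The section cites a previous study and names the software. It gives no SD, standardised effect, sidedness or test family.

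Three other places bear on this:

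- Primary outcome (Perceived pain) defines the VAS as a line from 0 to 100 mm.
- The last paragraph of the Introduction states the hypothesis: PNE added to the MR program improves pain more than the MR program with TBI. A comparison with the control group is then added. The Discussion opens with the same PNE contrast.
- Data analysis plans a 3x3 repeated-measures ANOVA at the 0.05 level and adds: "The Bonferroni test will be used for post hoc analysis".

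**The concern.** The paragraph has two faults and one ambiguity.

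1. **Detectable difference.** The assumption is 15 mm, but the power claim is attached to 5%. The base of the percentage is not defined. On the natural reading, 5% of a 100 mm scale, it is one third of the assumed effect.
2. **Contrast and alpha.** The 90% belongs to a two-group comparison of intervention with control at 0.05. The hypothesis concerns two active arms that share the same MR program, and the analysis plan judges pairs of arms after Bonferroni adjustment. The paragraph gives no power for that test.
3. **Loss to follow-up.** The text does not say whether 24 per group is the number needed for analysis or already contains the 20% allowance.

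At stake is what the trial can claim. A reader of the paragraph would expect 90% power for the planned comparisons, and even for differences as small as 5%. A non-significant PNE+MR versus TBI+MR result could then be given more weight as negative evidence than the design supports.

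**Working it through.** **Inputs from the article.** Difference 15 mm; scale 100 mm; alpha 0.05; power 90%; 24 per group, 72 in total; loss 20%; three arms, hence three pairs and a Bonferroni level of 0.05/3 = 0.0167.

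**Assumptions.** The SD is not stated, so it is solved back from the stated n. The test is taken as a two-sided two-sample t test with equal groups and no credit for within-subject correlation. Power comes from the noncentral t distribution with 2n − 2 degrees of freedom and noncentrality d·√(n/2), where d = difference/SD.

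**Step 1: the plan's own figure.** It cannot be reproduced without an SD. Two readings fit the text:

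- Reading A, 24 is the evaluable number. Power of 90% at 0.05 with n = 24 requires d = 0.956, so SD = 15/0.956 = 15.7 mm.
- Reading B, 24 already includes the loss. 19/0.8 = 23.75, rounded up to 24. Power of 90% at 0.05 with n = 19 requires d = 1.081, so SD = 15/1.081 = 13.9 mm.

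**Step 2: the 5% claim.** 15/100 = 15%, and 5% of the scale is 5 mm. With 24 per group at 0.05:

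- SD 15.7 mm: d = 5/15.7 = 0.319, noncentrality 0.319 × √12 = 1.10, power 19%.
- SD 13.9 mm: d = 5/13.9 = 0.360, noncentrality 0.360 × √12 = 1.25, power 23%.

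At SD 15.7 mm, 90% power for 5 mm would need about 208 per arm.

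**Step 3: the 15 mm difference at the Bonferroni level.** A 20% loss leaves 24 × 0.8 = 19.2, taken as 19 per arm.

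| Reading | SD (mm) | n per arm | Power at 0.05 | Power at 0.0167 |
|---|---|---|---|---|
| A | 15.7 | 24 | 90% | 79% |
| A | 15.7 | 19 | 82% | 67% |
| B | 13.9 | 24 | 96% | 89% |
| B | 13.9 | 19 | 90% | 79% |

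The fall from 90% to about 79% barely depends on the missing SD: it is the same whether the test was sized at 24 or at 19 per arm.

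**Step 4: sensitivity to the SD.** Power for 15 mm at 0.0167:

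| Assumed SD (mm) | 24 per arm | 19 per arm |
|---|---|---|
| 12 | 96% | 90% |
| 15 | 83% | 71% |
| 18 | 66% | 53% |
| 20 | 55% | 43% |
| 25 | 35% | 27% |

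**The case against.** A reader might infer that the trial's real power is 67–79% and that the plan ignores its own 20% loss. The article supports neither.

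- **No SD is given.** The 67–79% range follows only if 24 is the evaluable number and the test is a two-sided t test. The SD may have been left out when the protocol was condensed for the journal, and Step 4 shows how far the answer moves with it.
- **The loss is named.** Because 19/0.8 rounds up to 24, the stated n may already contain the allowance, and the word that opens the sentence on loss fits that reading. On the other side, the article calls 24 the number required and 72 the number included. The text is ambiguous, not silent.
- **Bonferroni is specified for post hoc tests only.** The ANOVA itself is at 0.05, and sizing a multi-arm trial on one key contrast at 0.05 is common. In a simplified single-timepoint check at d = 0.956, the three-group F test has 93% power with 24 per arm if the third arm equals either extreme, and 84% if it lies midway. With 19 per arm the figures are 85% and 73%. But an omnibus test cannot show that PNE+MR beats TBI+MR, so the pairwise test carries the hypothesis.
- **Repeated measures may change power.** If 15.7 mm is the SD of raw scores, a change-score contrast at 0.0167 with 19 per arm has about 50% power at a baseline–outcome correlation of 0.3, 67% at 0.5, 78% at 0.6 and 90% at 0.7. So 67–79% bounds power in neither direction.

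These points stand against any single figure for true power. They do not touch the 5% versus 15 mm conflict, or the mismatch of contrast and alpha.

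**Conclusion.** The point holds in this form. The 5% statement is wrong as written, or at best undefined: it conflicts with the 15 mm assumption, and read as 5 mm it has about 19–23% power, not 90%. The stated 90% is for a contrast and an alpha other than those on which the main hypothesis will be judged. Under the t-test assumptions above, Bonferroni power for 15 mm is 67–79% if 24 is the evaluable number and 79–89% if 24 already includes the loss. Neither reading reaches 90% for the adjusted comparisons.

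The figures also assume that the same 15 mm applies to PNE+MR versus TBI+MR, which the article does not state. What the article does not settle is the SD, the sidedness, the status of the 20% loss and the within-subject correlation. No one number should therefore be presented as the trial's power.

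**What to change.** Rewrite Calculation of the sample size and keep 72 patients:

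- replace the 5% phrase with 15 mm;
- state the SD taken from the cited study, and the test and sidedness used;
- say whether 24 per group is before or after the 20% loss;
- give power at the evaluable number for the contrast and alpha that will be used.

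Alternatively, name PNE+MR versus TBI+MR as the single primary contrast, tested at 0.05 with adjustment for baseline VAS, and state the power that follows. As an illustration, take d = 0.956 as the unadjusted effect (SD 15.7 mm, outcome-score SD) and divide it by √(1 − ρ²), where ρ is the baseline–outcome correlation. With 19 per arm, power is about 85% at ρ = 0.3 and 91% at ρ = 0.5. If the SD in the cited study is already that of change scores, this gain must not be counted again.

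The change is to text only and needs no extra patients. Its cost is that the stated power may become less favourable.

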### Intervention

The PaiNEd study will consist of 24 sessions lasting 8 weeks. The first intervention group will receive the PNE program and MR program. The second group will receive the MR program and TBI, provided in a pamphlet, on the management of pain and disability associated with side effects of cancer treatment. Finally, a control group will receive only the leaflet given to the second group.

#### First arm: PNE program + MR program. (PNE + MR)

For 8 weeks, patients will attend 60 minutes of supervised exercise and one manual therapy session with a duration of 30 minutes every 2 weeks.

#### Second arm: TBI + MR program (TBI+MR)

This intervention group will attend the same multimodal group as the previous one, but without access to the PNE intervention and receiving TBI in a leaflet format.

#### Third arm: Control group

This group will only receive TBI on the management of pain and disability associated with side effects of cancer treatment handed in a leaflet format. Once the measures are registered, they will be invited to participate in the multimodal program for ethical and moral reasons.

